**Secondary outcomes**		
Body image	QLQ-BR23 Body Image subscale [92]	• 4 items; 4-point Likert scale (1 ‘not at all’ to 4 ‘very much’)
		• Score: 0-100; higher score indicates higher level of functioning
		• Time frame: past week
		• Cronbach’s alpha: 0.69-0.91
Menopausal symptoms	FACT-ES ESS-18 [93]	• 18 items; 5-point Likert scale (0 ‘not at all’ to 4 ‘very much’)
		• Score range: 0-72; higher score indicates fewer menopausal symptoms
		• Time frame: past 7 days
		• Cronbach’s alpha = 0.79
Marital functioning	MMQ [84]	• 20 items; 9-point Likert scale (range 0-8)
		• Scales: marital adjustment (M); sexual adjustment (S); general life adjustment (GL)
		• Scale scores*: S + GL: 0-40; M: 0-80; higher score indicates greater dissatisfaction in the specific domain
		• Time frame: past 2 weeks
		• Cronbach’s alpha in normal vs. distressed group: M = 0.88/0.87; S = 0.64/0.82; GL = 0.60/0.68
Psychological distress	HADS [94,95]	• 14 items; 4-point Likert scale (range 0-3)
		• Subscales: depression (HADS-D); anxiety (HADS-A)
		• Total score: 0-42/Subscale scores: 0-21; higher score indicates more psychological distress
		• Time frame: past week
		• Cronbach’s alpha: HADS-A: 0.68-0.93; HADS-D: 0.67-0.90
Health-related quality of life	SF-36 [96,97]	• 36 items; dichotomous and 3- to 6-point Likert scales
		• Subscales: physical functioning; role limitations due to physical health problems; bodily pain; social functioning; general mental health; role limitations due to emotional problems; vitality; general health perceptions
		• Subscale score*: 0-100; higher score indicates higher levels of functioning/well-being
		• Time frame: past week
		• Cronbach’s alpha = 0.66-0.93 (mean: 0.84)
Sexual functioning (male partners)	IIEF [85]	• 15 items; 5-/6-point Likert scale (0-5 or 1-5)
		• Subscales: erectile function (EF); orgasmic function (OF); sexual desire (SD); intercourse satisfaction (IS); overall satisfaction (OS)
		• Total score: 5-75/Subscale scores: EF 1-30; OF 0-10; SD 2-10; IS 0-15; OS 2-10; higher score indicates a higher level of functioning in specific domain
		• Time frame: past 4 weeks
		• Cronbach’s alpha: 0.73-0.99

*The score is calculated based on weighted items.

FACT-ES ESS-18 = Functional Assessment of Cancer Treatment-Endocrine Symptoms, Endocrine Symptom Subscale; FSDS = Female Sexual Distress Scale; FSFI = Female Sexual Function Index; HADS = Hospital Anxiety and Depression Scale; IIEF = International Index of Erectile Function; MMQ = Maudsley Marital Questionnaire; PAIR Inventory = Personal Assessment of Intimacy in Relationships Inventory; QLQ-BR23 = EORTC breast cancer-specific quality of life questionnaire; SAQ = Sexual Activity Questionnaire; SF-36 = 36-Item Short Form Health Survey.

### Compliance with the internet-based CBT program

The level of compliance is established via a question that is posed to the sexologist at the completion of therapy: ‘How many of the total number of therapy sessions that you considered to be optimal for this client has the client actually completed?’. This question is answered on a five-point scale, ranging from ‘the client has done all of the sessions I deemed necessary (100%)’ to ‘the client has not/barely done the sessions I deemed necessary (less than 25%)’. Additionally, the actual number of completed modules and interventions are extracted from the client’s records at the mental health center where the internet program is housed. Additionally, at completion of therapy, both the client and the sexologist are asked to indicate the frequency with which homework assignments were completed on a five-point scale (always-frequently-occasionally-rarely-never), and to indicate the reasons for not completing all homework assignments, if applicable. Women who do not complete the internet-based CBT program are asked to indicate their reason(s) for discontinuation (e.g., therapy was too intensive, online therapy was not suitable, illness). Every effort will be made to obtain all questionnaires of all participants, regardless of whether they do or do not complete their therapy.

### Patients’ evaluation of the intervention program

Upon completion of the CBT, women in the intervention group are asked to complete an evaluation questionnaire about the program. Questions are posed about their satisfaction with the program, the perceived efficacy of the program in alleviating sexual problems, their satisfaction with the choice of modules and exercises, the usability of the program, if they would recommend the treatment to other women experiencing similar problems, and if they would suggest any changes to the program. Women who discontinue the CBT program are asked the same questions.

A subset of women (approximately 15 from the intervention group) will be asked to participate in an evaluation interview by telephone. This semi-structured interview covers the same topic areas as addressed by the self-report evaluation questionnaire, allowing women to provide feedback in a more narrative form. Where applicable, women will also be asked if their partner would be willing to share his or her experience with the program.

### Statistical issues

#### Power calculation

The SAQ, FSFI, FSDS-R and PAIR Inventory are the primary outcome measures on which sample size calculations are based. With a total sample of 130 women (65 per group), and under the assumption of no interaction, the study will have a 80% power to detect a 0.5 standard deviation difference (Cohen’s effect size [98]) for the main effects of the internet-based CBT program, with the p-value set at 0.05 (two-sided test). A 0.5 standard deviation difference is considered to be indicative of clinically meaningful differences in self-reported symptom experience [98].

We will recruit 160 women into the study, to allow for an attrition rate of approximately 20% (i.e., women who discontinue participation in the study entirely, including failure to complete all follow-up questionnaires). Those women who discontinue the therapy but complete the follow-up assessments will be included in the intention-to-treat analysis.

#### Statistical analysis

First, student’s t-tests or appropriate non-parametric statistics will be used to evaluate the comparability of the intervention and control group at baseline in terms of sociodemographic and clinical characteristics. If, despite the stratified randomization procedure, the groups are not comparable on one or more background variables, those variables will be employed routinely as covariates in subsequent analyses.

Questionnaire scores will be calculated according to published scoring algorithms. Between-group differences over time in mean scores will be tested using multilevel analysis. Effect sizes will be calculated using standard statistical procedures. All analyses will, to as great an extent as possible, be conducted on an intention-to-treat basis. Per protocol analyses will also be carried out (as a secondary analysis), comparing women who meet minimal compliance levels with the program with the control group. We will use correlation analyses to examine the relationship between degree of program adherence, partner involvement, and program effect. For the analysis of the secondary outcome measures, appropriate statistical (p value) adjustments will be made for multiple testing. The semi-structured interview data will be transcribed and content analyzed to extract narrative, qualitative information about the women’s experience with the intervention.

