### Recruitment and randomization

Patients are recruited from 10 community and university hospitals in the Netherlands and are identified through the hospital registries by their physician, or by means of the database of the Netherlands Cancer Registry. Selected patients are sent an invitation letter describing the study and internet-based therapy, and are asked to return a response card to indicate if they are interested in participation. In case of no interest, women are asked to specify their reason(s) for this on the card. In the absence of a response, a reminder is sent three weeks after the first mailing. Women who are not interested in participation or who do not respond to the reminder are not contacted again.

Interested women are screened for eligibility twice: first by a member of the study staff and subsequently by a sexologist. In these interviews, more information about the study procedures and therapy is given and eligibility criteria are checked. The sexologist carries out a diagnostic interview to determine final eligibility of the woman, and the Mini International Neuropsychiatric Interview [83] is completed. All sexologists involved in the study are female, and have undergone special training in the application of the internet-based CBT program.

Eligible women are sent a baseline questionnaire (T0) and an informed consent form. Study questionnaires can be completed online or in a paper-and-pencil format. The baseline questionnaire assesses sociodemographic and medical background variables, and the study outcomes. If the score of the marital adjustment subscale of the Maudsley Marital Questionnaire [84] (see ‘Study measures’ section) exceeds the cut-off score of 35, the eligibility of the participant is discussed once more with the sexologists to determine if the nature and severity of the relationship problems would recommend treating these problems prior to tackling the sexual dysfunction, thus resulting in exclusion from study participation.

Consenting women are randomized to either an intervention group (n = 80) or a waiting-list control group (n = 80) using the minimization technique, with type of surgery (breast conserving therapy; mastectomy only; mastectomy with breast reconstructive surgery), current endocrine treatment for breast cancer (yes; no), time since breast cancer diagnosis (<1 year; 1-3 yrs; 3-5 yrs), and menopausal status (premenopausal; postmenopausal) as stratification variables.

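### Covariates are selected by baseline significance tests, so chance imbalance rather than prognosis shapes the primary model, and the rule in effect never admits the four minimization factors

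*Protocol article*

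**What the plan says.** Under Recruitment and randomization, women are allocated 1:1 "using the minimization technique, with type of surgery" (three levels), current endocrine treatment (two), time since diagnosis (three) and menopausal status (two) as the balancing factors.

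Under Statistical analysis, the first step is that "student’s t-tests or appropriate non-parametric statistics will be used to evaluate the comparability of the intervention and control group at baseline". If, in spite of that allocation procedure, "the groups are not comparable on one or more background variables, those variables will be employed routinely as covariates in subsequent analyses". No significance level or other cut-off for comparability is given. Outcomes are then compared between arms over time by multilevel analysis, for which no covariates are named. The rule just quoted is the only one in the article that puts a covariate into a model.

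The Power calculation section states that with 65 women per group "the study will have a 80% power to detect a 0.5 standard deviation difference".

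**The concern.** A baseline test in a randomized trial asks whether chance produced the difference, and if allocation was done correctly the answer is known to be yes. The test therefore cannot show that the groups fail to be comparable. What it does is select variables by the size of a chance imbalance, whether or not they predict the outcome.

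The article's own Background shows the mismatch. It reports higher risk of sexual dysfunction after chemotherapy, yet chemotherapy is not a minimization factor. It would be adjusted for only if it happened to differ between arms, on the same footing as living situation.

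The minimization factors face the reverse problem. Minimization exists to keep them balanced, so a rule that admits only unbalanced variables shuts out the variables the design treats as important. If they are prognostic and the model omits them, the reported standard error counts between-arm variation that the allocation has already removed. It is then too large, and precision is lost.

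**Working it through.** **1. The plan's own figure.** Inputs from Power calculation: 65 per group, 0.5 SD, two-sided 0.05. The standard error in SD units is √(2/65) = 0.1754. Power = Φ(0.5/0.1754 − 1.96) = 81.3%, or 80.8% with the t distribution. The stated 80% reproduces. With about 20% attrition, 160 recruited gives 160 × 0.80 = 128, close to 130.

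**2. How often the rule adds a covariate by chance.** Sociodemographic and clinical data lists 5 sociodemographic and 8 clinical variables (date of diagnosis, five treatment types, medication use, comorbidity), 13 in all. Three (date of diagnosis, surgery, endocrine therapy) are tied to minimization, which leaves 10. Assuming independent tests at 0.05:

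- 10 variables: 1 − 0.95^10 = 40%
- Range: 1 − 0.95^5 = 23% for 5 variables; 1 − 0.95^15 = 54% for 15

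**3. Whether the rule can admit the minimization factors.** Trials of 130 women were simulated with the four factors, assumed level proportions, minimization with an 80% biased coin and 3,000 runs per scenario. At least one factor reached p < 0.05 in at most 0.03% of trials. With 10 other variables tested, at least one covariate was selected in 39–41%, in line with step 2.

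**4. Cost of omitting the factors when baseline scores are not used.** Let R² be the share of outcome variance that the factors explain. The article gives no value, so 0.1–0.2 is assumed. With perfect balance, true SE = √(1 − R²) × reported SE, and actual type I error = 2Φ(−1.96/√(1 − R²)):

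- R² = 0.1: 1.96/0.949 = 2.066, giving 3.9%
- R² = 0.2: 1.96/0.894 = 2.191, giving 2.8%

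The simulation, where balance is good but not perfect, used a single post-treatment score:

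| R² | Type I error without / with factors | Power at 0.5 SD without / with |
|---|---|---|
| 0 | 5.1% / 5.2% | 80.4% / 80.2% |
| 0.1 | 4.4% / 5.4% | 82.7% / 85.0% |
| 0.2 | 3.1% / 5.0% | 82.9% / 88.3% |

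At R² = 0.2 with no true effect, the model without factors reports a mean SE of 0.175 against a true SD of the estimate of 0.158. With factors the two agree at 0.157. The mean estimate stayed at the true value with and without the factors.

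**5. The same cost when T0 is used.** Both arms are measured at T0, T1 and T2. Suppose the factor effects are the same at each time.

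- In a change score they cancel exactly, so nothing is lost.
- In a model adjusted for the baseline score, with baseline–follow-up correlation ρ, the factors explain R²(1 − ρ)/(1 + ρ) of the residual variance.

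The least favourable case of R² 0.1–0.2 and ρ 0.5–0.7 (assumed) is R² = 0.2, ρ = 0.5:

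- Share: 0.2 × 0.5/1.5 = 0.067
- Type I error: 2Φ(−1.96/√0.933) = 4.2%
- Reported SE: 0.1754 × √0.75 = 0.1519; true SE: 0.1519 × √0.933 = 0.1468
- Power without factors: Φ((0.5 − 1.96 × 0.1519)/0.1468) = 91.6%
- Power with factors: Φ(0.5/0.1468 − 1.96) = 92.6%

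Simulation over the same ranges agrees: type I error of about 4–6%, and a power gain from the factors of about 0–1 point.

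**The case against.** The strongest reply is that the covariate rule is a safeguard against unexpected imbalance, fixed in advance, blind to outcomes and applied to all later analyses alike. It is not selective adjustment. A journal article need not list every model term, and a fuller plan may already include the minimization factors. The multilevel analysis over time probably uses T0, which removes most of the precision argument. Even without T0, power stays above the promised 80%.

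Much of this stands. A reader might infer that the protocol excludes the minimization factors. It does not say so; their absence is the effect of the only rule stated. A reader might also infer bias or too many false positives. The working shows neither: the estimate is unbiased and the error is conservative. The 40% is the chance that a covariate is added, not an error rate. It also rests on independence between variables that clearly overlap, such as relational status and living situation.

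Two things do not fall. The rule is a positive instruction, so a fuller plan would have to overrule it, not merely add detail. And the article does not say how T0 enters the model. Its power statement speaks of main effects with no interaction, so the small-loss case is likely but not assured.

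**Conclusion.** The point holds as a flaw in a stated rule. Baseline tests decide the covariates of every later analysis. Under the stated assumptions they add at least one by chance in about 40% of trials (23–54% for 5 to 15 variables), with no cut-off to make the step reproducible. In practice the rule never admits the four minimization factors.

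The consequence for inference is modest and conservative. For R² of 0.1–0.2, leaving the factors out costs 2–5 points of power, with a type I error of about 3–4%, if baseline scores are ignored. It costs about 0–1 point if T0 is used and factor effects do not change over time. It vanishes if the factors are not prognostic; the Background itself calls the evidence on surgery and endocrine treatment mixed. Factor effects that change over time would restore part of the loss.

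The documents do not support a claim that the trial is underpowered or its primary test invalid. The case for change is that the model should be fixed before the data are seen and should reflect the allocation, at almost no cost.

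**What to change.** - Delete the baseline significance tests and the covariate rule that depends on them.
- State in advance that every primary and secondary model includes surgery type, current endocrine treatment, time since diagnosis and menopausal status, plus the baseline score of the outcome, either as a covariate or through the T0 measurement in the multilevel model. Say which.
- Present baseline characteristics by arm descriptively.
- Label any adjustment for other imbalances as a sensitivity analysis.

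The cost is wording and about six degrees of freedom for the factors (2 + 1 + 2 + 1), against 130 or more women. The factors are already needed for allocation and the outcomes are already measured at T0, so no new data are required. The sample size and the stated 80% power stay as they are.

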### Study arms

#### Intervention group: internet-based CBT program

Each woman is assigned a sexologist who guides her through the internet-based CBT program. Contact with the therapist is web-based, via a secured, password-protected website. From a total of 10 modules, the sexologist selects four to five modules that best fit the sexual problems of the client. The internet-based CBT program was originally developed for use in the general population at Virenze, a mental health center located in Utrecht, the Netherlands. The program was adapted for use specifically for breast cancer survivors. This involved editing and adding text related to the physical and psychosexual problems often experienced by women who have had breast cancer. The therapists are licensed psychologists and sexologists who have undergone additional training in issues relating to breast cancer, and in the use of the internet program.

A description of the content of the different program modules is provided in Table 1. Each module contains several interventions, each of which comprises the following elements: (1) introduction, (2) psycho-education, (3) “homework” assignments (e.g., registration exercises; discuss intimacy with partner; sensate focus exercises) and (4) reporting back to the therapist and receiving feedback on the homework assignments. The modules can be used in varying order, leading to a tailored and flexible treatment program consisting of a maximum of 20 therapy sessions that are completed within a period of 24 weeks. A minimum of five sessions is considered the lower limit of sessions required in order to expect an effect. The average time investment for a participant is 90-120 minutes per week. Women are motivated by the sexologist to involve their partner in the treatment, but partner involvement is not mandatory. The time limit within which the therapist should respond to incoming messages from a client is set at five working days. Weekly contact between therapist and client is pursued. After 10 weeks of treatment, a mid-term evaluation is held to reflect on the progress so far, and to adjust goals, if necessary, for the remaining part of treatment. The internet-based CBT program is provided at no cost to the woman.

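### The secondary per-protocol contrast sets compliers from one arm against all controls, so selection could bias it in either direction; a complier average causal effect would answer the question better

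*Protocol article*

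**What the plan says.** The Statistical analysis section makes intention-to-treat the main basis: "All analyses will, to as great an extent as possible, be conducted on an intention-to-treat basis". It adds per-protocol analyses, labelled secondary, "comparing women who meet minimal compliance levels with the program with the control group". It states no restriction on the controls and no adjustment for selection into compliance, and it does not name the measure behind the compliance levels. It also plans correlations between adherence, partner involvement and program effect.

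Three other statements bear on what compliance could mean:

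- Compliance section, therapist rating: "The level of compliance is established via a question that is posed to the sexologist at the completion of therapy". The question reads "How many of the total number of therapy sessions that you considered to be optimal for this client has the client actually completed" and is answered on a five-point scale.
- Compliance section, records: in addition, "the actual number of completed modules and interventions are extracted from the client’s records". Homework frequency is also rated by client and sexologist.
- Intervention group section: "A minimum of five sessions is considered the lower limit of sessions required in order to expect an effect".

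**The concern.** Randomization makes the two full arms comparable. It does not make a self-selected part of one arm comparable with all of the other. Women in the control group who would have dropped out of the program cannot be identified, so they stay in the comparison while their counterparts in the intervention arm are taken out. The planned baseline check compares the two randomized groups, not this subset.

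A link between compliance and prognosis is plausible on the article's own account, since illness and finding the therapy too demanding are among its example reasons for stopping.

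The therapist's rating could add a second link. It is made once therapy is over, by the person who delivered it, against a session total she set herself. A woman who did well on few sessions can be rated fully compliant. A woman who did badly on the same number can be rated as falling short.

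At stake is the reading of the secondary result. A per-protocol estimate above the intention-to-treat estimate invites the interpretation that it is the effect of proper use, although part of it may be selection. The planned correlation of adherence with program effect within the treated arm is open to the same confounding.

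**Working it through.** **Inputs.** From the Power calculation section: 65 analysable women per group, 0.5 SD, 80% power, two-sided 0.05, 160 recruited. From the Statistical analysis section: compliers against the control group. Assumed, because the article gives neither: the share p of intervention women who comply, and the correlation rho between the tendency to comply and the outcome that remains after any baseline adjustment.

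**Step 1: the plan's own figure.** A two-sample t-test with 65 per group and 0.5 SD has power 0.808 (0.813 by the normal approximation). 130/160 = 81.25%, so recruitment allows for 18.75% attrition, in line with the stated 20% or so. The design figure reproduces. The plan gives no figure for the per-protocol contrast.

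**Step 2: bias with an inert program.** Let the outcome be standard normal in both arms, and let compliers be the top share p of a score correlated rho with the outcome. The control mean is 0, so

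bias = rho × φ(z) / p, where z is the (1 − p) normal quantile and φ is the normal density.

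Example: p = 0.70 gives z = −0.524, φ(z) = 0.348 and φ(z)/p = 0.497. With rho = 0.3 the bias is 0.3 × 0.497 = 0.149 SD.

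**Step 3: false-positive rate.** 20,000 simulated trials per cell, 65 per arm, t-test of compliers against all controls. Each cell gives bias in SD (formula), then two-sided rejections at 0.05 (simulated).

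| Compliers | rho 0.2 | rho 0.3 | rho 0.4 |
|---|---|---|---|
| 80% | +0.070; 6.6% | +0.105; 8.9% | +0.140; 12.1% |
| 70% | +0.099; 8.1% | +0.149; 11.6% | +0.199; 17.6% |
| 60% | +0.129; 9.6% | +0.193; 15.5% | +0.258; 24.4% |

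Relative to the 0.5 SD target this runs from 0.070/0.5 = 14% to 0.258/0.5 = 52%. Intention-to-treat on the same data rejected in 4.7% to 5.2% of trials across all scenarios run.

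**Step 4: outside that range.** With rho = 0 the bias is zero and rejections stay near 5% at every share. With rho = −0.2 the bias is −0.04 SD at 90% compliers and −0.16 SD at 50%. With rho = 0.5 and 50% compliers it is +0.40 SD, with 46.9% rejections.

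**Step 5: what the alternative does.** The complier average causal effect is the intention-to-treat effect divided by p.

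- Inert program: 0/p = 0, whatever rho is.
- True effect of 0.5 SD in compliers, none in others, p = 0.70, rho = 0.3: intention-to-treat is 0.70 × 0.5 = 0.35. The complier estimate is 0.35/0.70 = 0.50. The naive contrast is 0.50 + 0.149 = 0.65.

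So exceeding the intention-to-treat result is not in itself a sign of bias. The excess over 0.50 is.

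**The case against.** The strongest reply has four parts.

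- *The direction is not known.* A reader might infer that the analysis would show benefit even for an inert program. The article does not support this. A positive bias needs a positive correlation between compliance and prognosis, which the article does not give, and Step 4 shows zero or negative bias under other assumptions. This part stands: the right word is could. An unknown direction is still no reason to rely on the contrast.
- *The therapist's rating may not be the measure.* A reader might also infer that this rating defines the per-protocol group. The Compliance section does name it first, but the Statistical analysis section does not say which measure applies. Record counts and a five-session minimum are also in the article, and the cut-off may sit in a fuller document. This stands too: the missing cut-off is no finding, and the worry about the rating applies only if it is used. The one-sided exclusion remains whichever measure is chosen.
- *The harm is contained.* The analysis is labelled secondary, women who stop therapy but complete follow-up stay in the intention-to-treat analysis, and the correlations carry no causal claim. This stands, and it limits the weight of the point.
- *The simulation uses raw outcomes, whereas the plan models change over time.* This stands in part. Baseline adjustment removes selection that acts through baseline level, so rho must be read as what is left. The bias is then in units of the adjusted SD, which is smaller than the raw SD, so the comparison with 0.5 SD is an upper reading. Prognosis that baseline scores do not capture is not removed.

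**Conclusion.** The point holds in a limited form. The per-protocol contrast is not protected by randomization and could show a spurious effect in either direction. For 60-80% compliers and a remaining correlation of 0.2-0.4, both assumed, the bias is about +0.07 to +0.26 SD. It is zero without correlation, and negative if women who improve early stop sooner and count as non-compliant.

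The intention-to-treat conclusion is unaffected, so a reader should not infer that the trial's main result is in doubt. This is a cheap improvement to a secondary analysis, and worth making before the data are analysed.

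**What to change.** 1. Estimate the effect in compliers at T1 and T2 as a complier average causal effect, with randomization as the instrument. The design allows it: controls are offered the program only after T2, and questionnaires are sought from women who stop therapy.
2. Define compliance in advance from the program records, not from the therapist's rating. The article says the records yield completed modules and interventions, so a prespecified mapping to the five-session minimum is needed.
3. Keep any naive per-protocol contrast only as a supportive, non-randomized result, and report the adherence correlations as descriptive.
4. State the exclusion restriction: assignment has no effect in women below the threshold. The five-session statement supports this but does not prove it, because in an open waiting-list trial with self-reported outcomes a few sessions, or assignment alone, may change answers. If it fails in that way, the complier estimate is inflated. A sensitivity analysis that counts any session as compliance addresses the first possibility; an effect of assignment alone would remain.

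**Cost.** Some wording, the mapping and one extra model. The interval widens. With 65 per arm and 70% compliers (0.70 × 65 = 45.5, taken as 46), rough standard errors are √(2/65) = 0.175 SD for intention-to-treat, √(1/46 + 1/65) = 0.193 SD for the naive contrast, and 0.175/0.70 = 0.251 SD for the complier effect. The 95% half-widths (× 1.96) are about 0.34, 0.38 and 0.49 SD.
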